### *Low Urinary tract assessments*

- Neurogenic Bladder Symptom Score (NBSS): comprises 23 questions covering 3 domains, including incontinence (primary outcome, AIM 3A), storage & voiding, and specific consequences, as well as one question on QoL.
- The Incontinence-QoL (I-QoL): comprises 10 questions covering 3 domains, including avoidance and limiting behaviour, psychosocial impacts, and social embarrassment, which will be summarised as a total score. All scores, for each domain and a total, will be transformed into a continuous scale value.

### *Bowel assessments*

- Neurogenic bowel dysfunction score (NBD Score) The NBD score is a measure of both constipation and fecal incontinence and was developed for and validated in the SCI population. This questionnaire comprises 10 questions focusing on defecation (i.e., frequency, duration, and clinical symptoms), constipation (i.e., use of aiding medication and digital stimulation), fecal incontinence (i.e., frequency, aiding medication, and flatus; and peri-anal skin problems. The consequential NBD score relates to four different neurogenic bowel dysfunction severity levels
- The modified Wexner fecal incontinence score (WIS): The WIS scale includes items that take into account type, frequency and extent to which fecal incontinence alters an individual's life, use of anti-diarrhea medications and the ability to defer defecation for 15 min.
- Time Needed for Bowel Movement: Participants will be asked to record the time from 'suppository insertion' to 'when bowel evacuation is completed', during their regular bowel movement at home.

### *Sexual health assessments*

- The International Index of Erectile Function (IIEF-15) (male participants): comprises of 15 questions covering five domains, including erectile function, orgasmic function, intercourse satisfaction, and overall satisfaction.
- The Female Sexual Function Index (FSFI) (female participants): comprises of 19 questions covering six domains, including desire, arousal, lubrication, orgasm, satisfaction and pain.
- Pregnancy test for female participants: A pregnancy test will be required for any female participants of child bearing potential to ensure the participant is not pregnant.

### *Cardiovascular assessments*

- Autonomic dysfunctions in SCI (ADFSCI) questionnaire: Comprises of 21 questions, covering three domains, including general, medications, and autonomic dysreflexia symptoms and severity
- 24 hrs diary of activities: Participants are given a diary to log their activities while wearing the 24 hour blood pressure monitor.

### *Semi-Structured Qualitative Interview*

Participants will be interviewed in person by a sexual medicine clinician at the Blusson Spinal Cord Injury Centre to ascertain qualitative information on sexual functioning. These interviews will be digitally recorded, transcribed verbatim and anonymized on completion. The interview schedule will include questions pertaining to the following: participants sexual history and current relationship status, level of

sexual drive, ability to orgasm, barriers to sexual activity, self-esteem, the use of ergogenic aids, and participants' perceptions of the role of TCSCS on sexual functioning. Female participants will be asked about lubrication quality, and male participants will be asked about erection quality (with and without pharmaceutical or prosthetic assistance), and their ability to ejaculate. Participants will be advised during the consent process that the clinician will be acting as a researcher during this interview and is therefore prohibited from providing clinical care or direct medical advice during the study. A complete thematic analysis will be performed using NVivo software (Version 9.0, QSR, Southport, UK). The expected duration of the interview will be approximately 30 – 45 minutes.

#### Known Study Risks/Harms

- Through the period of study, any adverse event will be recorded using the adverse event report form in section 9 of the application. If an adverse event occurs during the testing session will be immediately stopped. In addition, the participant's primary care provider and UBC CREB will be notified as necessary if serious adverse events (SAEs) occur. In addition, the participant's primary care provider, UBC CREB, and the Data Monitoring Committee (DMC) will be notified as necessary if serious adverse events (SAEs) occur. A Data and Safety Monitoring Committee will comprise of 3 individuals external and independent to the study to review the adverse event reports and stop the study if the safety data are of sufficient concern. Any adverse effects will be reported to these individuals responsible for Data and Safety Monitoring Committee, as well as to the appropriate UBC ethics boards by the study coordinator.
- The urodynamics and ARM procedure will necessitate that the participant expose their genitals in the presence of the Principal Investigator or study health care professionals. Every effort will be made to ensure their comfort and privacy during the procedure as long as safety is assured. For the urodynamic assessment, once the catheter is implanted, the gown will be placed to cover their genitals. Due to the risk of high blood pressure, participants will not be left unattended during urodynamic assessments.
- Participants may experience stress as a result of answering questions related to symptoms of depression, bowel and bladder function, and sexual functioning/satisfaction. The depression, bowel and bladder function questionnaires used in this study are commonly used clinical screening tools. The sexual functioning/satisfaction questionnaires were carefully chosen as they have previously been used in individuals with SCI. These questionnaires will be delivered in a private setting, by a single sexual medicine clinician, with considerable experience delivering these assessment tools and discussing such sensitive topics with male patients with SCI. Participants will also be provided with the Fraser Health Crisis line in the informed consent document if they require immediate, free and confidential emotional support.
- Participants will be advised not to take Viagra, Clans or Levitra for 4 days before the urodynamic tests as this could cause a drop in blood pressure requiring medical attention.
- With TCSCS we do not expect adverse events as our study will only utilize parameters and electrodes approved in previous studies. Stimulation could potentially irritate the skin, so we will monitor skin temperature for potential irritation. TCSCS elicit AD, however so far no AD/OH is observed in TCSCS studies. Furthermore, cessation in stimulation immediately reduces blood pressure, and we will be monitoring blood pressure closely during procedures. In case of adverse

events, the participant's primary physician would be notified as needed. Participants will be continuously monitored for any signs of risks or discomfort. As mentioned, we will also continuously monitor cardiovascular signals such as blood pressure and heart rate. For TCSCS, we will additionally measure skin temperature.

- In this study, participants will be asked to undergo UDS, a clinically approved procedure for examination of urinary bladder function in participants with injury to the central or periphery nervous system. This procedure is typically recommended to be performed on a biannual basis in participants with multiple sclerosis, stroke, and SCI, in order to establish urine bladder function. It is known that within the SCI population, UDS commonly elicits episodes of AD in participants with injury at the T6 spinal segment and above (an inclusion criteria for the present study). Clinically, UDS is an important component of bladder function evaluation following SCI. Risk management in this study involves having trained personnel performing these studies in a clinical facility with protocols in place to manage iatrogenic/artificially induced episodes of AD. All these criteria are in place at the site of the Principal Investigator, located at the ICORD/Blusson Spinal Cord Injury Centre at the Vancouver General Hospital.
- Concentric needle EMG is a common clinical procedure, performed in a variety of clinical settings worldwide. The risks of EMG are very small and include small risk of bleeding, bruising and mild discomfort that can last up to 24 hours. EMG is very well tolerated and the risks will be minimized by localizing the target muscles using well-established surface anatomical landmarks in order to avoid placement in proximity to blood vessels or nerves. In the event of discomfort during the procedure, this will be minimized simply by moving the needle to a slightly different position.

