### Statistical Plan

Statistical analysis on LUT, bowel and sexual function will be performed (n = 40 with SCI).

A sample size calculation was performed using G\*power, version 3.0.10, with power set at 0.8 and  $\alpha$  at 0.05. Data from participants that match our inclusion criteria (n = 5, level of lesion C5 – T10, motor-complete AIS, A or B) were used from a recent TCSCS study. A minimum sample of 26 participants is required to detect a significant change in voiding efficiency [voided volume / (voided volume + post-void residual volume)] with short-term TCSCS (stim-off =  $37.8 \pm 40.6\%$  vs. stim-on =  $58.2 \pm 39.4\%$ , effect size = 0.510). Presently, there are no long-term TCSCS data with LUT and bowel outcomes, consistent with those proposed in this protocol, to facilitate a meaningful power calculation. Therefore, given this is a pilot trial study, and in order to account for drop out with long-term TCSCS, we aim to investigate 40 individuals with SCI (n = 40, C5 – T6). Short-term TCSCS effects on UDS parameters (AIM 2A) as well as ARM testing (AIM 2C) with or without different stimulation configurations will be assessed using a repeated measures non-parametric analysis of variance (ANOVA), i.e. Kruskal–Wallis test. Data from the repeatability portion of the study (AIM 2A) will be assessed within (same session) and between (different sessions) visits (2 and 3) using a repeated measures non-parametric ANOVA. TNFBM will also be assessed using a repeated measures non-parametric ANOVA.

Long-term TCSCS: Differences in continuous variables for questionnaire data (NBSS, NBD Score, I-QoL, IIEF-15 or FSFI) in AIM 3 will be assessed using a two-way repeated measures [baseline, immediately post long term TCSCS as well as post-interventional follow up at 6 and 12 weeks] ANOVA comparing changes between moderate and intensive TCSCS. Furthermore, UDS testing as well as 'faecal continence severity' (baseline and end of TCSCS 6-week period) will be assessed using Wilcoxon signed-rank tests within

groups. A P-value less than 0.05 will be considered statistically significant. A complete thematic analysis will be performed to collect contextual qualitative data from the sexual health interview.

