### Urodynamics

Participants will undergo standard clinical procedures for UDS, including cystometry with water at 21°C and a filling rate of < 30 mL per minute through a 6F double lumen catheter with the participants in the supine position. Abdominal pressure will be measured with a 10F intrarectal balloon catheter. Pelvic floor electromyography will be recorded during cystometry with a surface electrode placed on the

perineum. Filling will be stopped when the participants report a sensation of fullness, at the moment of urine leakage, if blood pressure reaches levels of 180/110 mmHg, or per the request of the patient.

Following the standard clinical assessment UDS we will perform UDS with TCSCS. To assess the efficacy of short-term TCSCS' on LUT function, we will first prefill the bladder (i.e. 50-75% of cystometric capacity from the first UDS) without eliciting detrusor overactivity or autonomic dysreflexia. Then, TCSCS (as described above) will be delivered for 60 s each interspersed with 30 s rest (i.e. no stim) to optimize the configuration for each individual. Stimulation frequency and location will be guided by the results of the Baseline EMG Mapping of Spinal Cord Segments performed during visit 3.

TCSCS will be stopped when the participants report a sensation of fullness, at the moment of urine leakage, if blood pressure reaches levels of 180/110 mmHg, or per the request of the patient.

Urodynamics will be performed by a trained clinician (MD or RN) under the supervision of [name] (MD), who is a urologist.

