#### Cardiovascular monitoring

Cardiovascular monitoring will be utilised as a safety measure to detect and record potential ACVEs. such as autonomic dysreflexia, during UDS and ARM (with and without TCSCS). BP will be measured continuously (beat-by-beat) via finger photoplethysmography corrected to brachial pressure and heart rate, measured via one-lead electrocardiogram. An attending physician will monitor for potential development of episodes of autonomic dysreflexia, which is defined according to the International Standards to document remaining Autonomic Function after SCI as an increase in systolic blood pressure  $\geq 20$  mmHg from baseline. Autonomic dysreflexia will be resolved with the implementation of an established clinical management protocol in accordance with the Consortium of Spinal Cord Medicine Clinical practice guidelines (Clinical Practice guidelines provide recommendations for healthcare specialists based on evidence-based research conducted by the Consortium for Spinal Cord Medicine).

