#### Treatment

Non-pharmacological components for management of AD episodes include the following:

1. When an episode of AD is confirmed, the first recommended step is to sit the participant upright or elevate the head of the bed in an attempt to induce an orthostatic decline in blood pressure. Additionally, loosen or remove all restrictive clothing and devices that could be triggers of painful stimuli (tight belt, shoe lace, orthotics on the leg, etc).
  - After this step measure blood pressure - this step could be sufficient to eliminate the episode of AD. If blood pressure is still elevated go to step 2.
2. Check the urinary bladder. If the catheter is inserted or kinked; establish urine outflow.

- After this step measure the blood pressure again and if the blood pressure is still elevated go to step 3.
3. Check for possible fecal impaction (use lidocaine gel to decrease irritation).
    - After this step measure the blood pressure again and if the blood pressure is normalized and symptoms subside, AD is successfully managed.
    - However, if arterial blood pressure is still elevated and it is above 150 mmHg the next step in management is initiation of pharmacological agents.

Based on literature and recommendations, the present pharmacological arsenal for management of AD episodes in North America includes the following:

1. Nifedipine (5mg capsule)
2. Captopril (25mg capsule)
3. Nitrates (1-2 inches applied to non-hairy part of chest)

These recommendations were developed and based on the consensus of specialists who were involved in development of PVA guidelines for management of AD following SCI.

The costs of all tests, examinations, and medical care required as a part of this study will be provided at no cost to the study subject. The subject and others may benefit from the overall conclusions to be drawn from the results of this study. Participation in this study could provide further data on the impact of TCSCS on lower urinary tract, bowel and sexual function following SCI.

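### The stop-on-adverse-event rule conflicts with the urodynamics procedure, so the stimulated run may be selectively missing, or sometimes follow a blood-pressure drug, in dysreflexia-prone participants

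*Protocol*

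**What the plan says.** Five parts of the protocol bear on what happens after dysreflexia in the unstimulated run.

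- **Known Study Risks/Harms**, on adverse events: "If an adverse event occurs during the testing session will be immediately stopped". The sentence lacks a subject, but its natural reading is that the session stops. It gives no severity threshold, no exemption for expected events and no rule for resuming.
- **Cardiovascular monitoring**: monitoring is there "to detect and record potential ACVEs. such as autonomic dysreflexia, during UDS and ARM (with and without TCSCS". Dysreflexia is "defined according to the International Standards to document remaining Autonomic Function after SCI as an increase in systolic blood pressure" of at least 20 mmHg from baseline, and is to be resolved under a clinical management protocol.
- **Urodynamics**: filling ends at fullness, leakage, 180/110 mmHg or the participant's request, and the same limits end stimulation. On the order of runs: "Following the standard clinical assessment UDS we will perform UDS with TCSCS". No condition is attached for an earlier episode.
- **Treatment**, under the management of dysreflexia: three non-drug steps come first. Then "if arterial blood pressure is still elevated and it is above 150 mmHg the next step in management is initiation of pharmacological agents".
- **Known Study Risks/Harms**, on urodynamics: "UDS commonly elicits episodes of AD in participants with injury at the T6 spinal segment and above". Injury at or above T6 is an inclusion criterion, so this covers everyone enrolled.

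Objective 2 asks whether short-term stimulation is safe with respect to dysreflexia, and Hypothesis 2A predicts improvement without adverse cardiovascular events. The Statistical Plan sizes the short-term comparison: "A minimum sample of 26 participants is required to detect a significant change in voiding efficiency", with 40 to be enrolled.

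**The concern.** The order within a urodynamics visit is fixed: unstimulated first, stimulated second. The randomised pathways only exchange the order of the urodynamics and manometry visits, so they cannot balance anything that the first run does to the second.

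If the adverse-event rule is applied as written, a participant with dysreflexia in the unstimulated run does not reach the stimulated run at that visit. If the Urodynamics section is applied as written, the same participant does reach it, possibly after a blood-pressure drug. Staff following the protocol could do either, and the choice bears on the people most liable to the safety event under study.

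Two things are at stake. First, a short-term finding of no adverse cardiovascular events during stimulated urodynamics could be drawn mainly from people who had none without stimulation. Second, the number of complete off-on pairs could fall.

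**Working it through.** **1. Do the rules conflict?** For one event, dysreflexia in the unstimulated run, the passages say:

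| Section | What ends | What follows |
|---|---|---|
| Known Study Risks/Harms | The testing session, on any adverse event | Nothing stated |
| Urodynamics | Filling (or stimulation), at 180/110 mmHg, fullness, leakage or request | Stimulated run, unconditionally |
| Cardiovascular monitoring | Nothing stated | Episode is managed; continuation not mentioned |
| Treatment | Nothing stated | Non-drug steps, then possibly a drug; continuation not mentioned |

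The conflict is between the first two rows. The last two are compatible with either.

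The thresholds show it too. The definition of dysreflexia is met at baseline systolic + 20 mmHg. The systolic filling limit is 180 mmHg. For any baseline below 180 - 20 = 160 mmHg, the definition is met before that limit. If each such rise ended the session, the systolic limit would seldom be what stopped a fill, so the two sections do not describe the same conduct.

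**2. What can happen to the stimulated run?** There are three outcomes: not done; done without a drug, because the episode resolved by non-drug steps (the protocol says the first step may be enough); or done after a drug, if pressure stayed above 150 mmHg and testing went on. The protocol does not say which are intended.

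**3. The plan's own figure.** Inputs from the Statistical Plan: stim-off 37.8 ± 40.6%, stim-on 58.2 ± 39.4%, effect size 0.510, power 0.8, alpha 0.05, minimum 26.

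- Difference: 58.2 - 37.8 = 20.4 points.
- Paired effect size: dz = 20.4 / √(40.6² + 39.4² - 2r × 40.6 × 39.4). With r = 0.5 (assumed; not stated), dz = 0.510, as in the plan.
- Paired t-test, noncentral t, dz = 0.51: one-sided alpha 0.05 needs n = 26 (power 0.812), which reproduces the plan. Two-sided would need 33, and 26 then gives power 0.705. The plan does not state sidedness.

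**4. Illustration of lost pairs.** Each participant has two urodynamics visits, so a participant drops out of the off-on comparison only if the stimulated run is lost at both. Let f be that share. No figure for f is given, so the range is an assumption. Pairs = 40 × (1 - f).

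| f | Pairs | Power, one-sided | Power, two-sided |
|---|---|---|---|
| 0 | 40 | 0.936 | 0.882 |
| 20% | 32 | 0.880 | 0.798 |
| 35% | 26 | 0.812 | 0.705 |
| 50% | 20 | 0.710 | 0.581 |
| 70% | 12 | 0.505 | 0.365 |

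The stated minimum is reached at 40 - 26 = 14 participants lost (14/40 = 35%) and missed beyond that. The selection problem does not depend on crossing that line, because the lost runs would come from dysreflexia-prone participants at any f above zero.

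**The case against.** The strongest reply is that treating an episode and stopping the session are compatible, and that the stop rule is one ungrammatical sentence about a testing session, not a visit. The protocol never says that an expected rise during urodynamics triggers it, and treats such episodes as a known effect with on-site management. This has force: the rule may not have been meant for every 20 mmHg rise. But the protocol names dysreflexia as an adverse cardiovascular event in unstimulated runs and gives the stop rule no threshold. The ambiguity is the defect.

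Several stronger readings are tempting but not supported:

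- *The treatment sections let the visit go on.* They are silent on continuation; it is the Urodynamics section that carries the visit forward.
- *The stimulated run must be either missing or medicated.* Drug-free resolution followed by a drug-free run is possible.
- *Anyone who misses the run is never tested under stimulation.* All participants receive it at the mapping visit. Those in the long-term phase have 12 or 30 sessions with blood pressure taken every minute, plus two 24-hour recordings during treatment. The gap concerns the stimulated urodynamics run.
- *A drug effect would show as a significant on-off difference in dysreflexia.* The Statistical Plan names no such test. The runs are also not alike: the stimulated one starts from a prefill of 50-75% of capacity, chosen to avoid provoking dysreflexia.
- *Manometry is equally affected.* The statement that dysreflexia is common concerns urodynamics only.

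It is also fair that handling medicated or missing runs in the analysis commonly belongs in a statistical analysis plan, which is not shown. Whether the second run takes place is trial conduct, however, and an analysis plan cannot recover runs performed inconsistently or drug times never recorded.

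**Conclusion.** The point holds in a limited form. The session stop in Known Study Risks/Harms and the fill-only stop with an unconditional stimulated run in Urodynamics cannot both be followed after dysreflexia in the unstimulated run, and the treatment sections do not settle the matter. Because that run always comes first and dysreflexia is called common, the stimulated run may be selectively missing, or sometimes follow a drug, in dysreflexia-prone participants. The short-term conclusion of Objective 2 on adverse cardiovascular events would then rest on a selected remainder.

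The size cannot be fixed from the protocol. The 35% threshold assumes loss at both urodynamics visits and uses the plan's minimum as a yardstick; the power figures also assume a paired t-test at effect size 0.51. How many episodes would reach the drug step is unknown. A reader might infer that medicated runs must be excluded. The documents do not call for that, and exclusion would itself remove dysreflexia-prone participants.

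**What to change.** 1. Reconcile Known Study Risks/Harms with Urodynamics, Cardiovascular monitoring and Treatment, so that the protocol says one thing about whether the stimulated run follows dysreflexia in the unstimulated run. Say whether an expected episode during urodynamics counts as an adverse event for the stop rule. The clinical choice is the investigators'.
2. Record any blood-pressure drug given during the visit, with its time.
3. Report dysreflexia during stimulated urodynamics against everyone who began the visit. Cross-tabulate dysreflexia in the unstimulated run (yes or no) by the stimulated run: done drug-free, done after a drug, or not done. Runs not done are then not read as event-free.

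The cost is protocol wording, one case-report field and one table. No change to sample size or visit schedule is implied.

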### *Visits 4,5,6: Urodynamics and Anorectal Manometry – Weeks 4-6:*

Approximately 2.5 hours per visit.

Following Visits 1 (Screening) Visit 2 (baseline assessments) and Visit 3 (mapping visit) using a randomized counter-balanced approach, all individuals will be allocated into two distinct pathways:

- Pathway #1: individuals will start with Urodynamics, (UDS 1, Visit 4), followed by a second session of Urodynamics (UDS 2, Visit 5), and ARM (Visit 6).
- Pathway#2: individuals will start with ARM (Visit 4), followed by Urodynamics (UDS 1, Visit 5), and a second session of Urodynamics (UDS 2, Visit 6)).

TCSCS and Cardiovascular monitoring will be performed during UDS and ARM. Please see Description of Assessments for details of Urodynamics, ARM, TCSCS and Cardiovascular monitoring.

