### *Visits 7 – 18 or 36: Long Term TCSCS – Weeks 7-12:*

Approximately 90 minutes per visit.

Participants will come to ICORD for long term TCSCS, either 2 days/week (moderate) or 5 days/week (intense) for 6 weeks for a total of either 12 sessions or 30 sessions. Please see Description of Assessments for the details of an individual session.

During the 6 weeks of long term TCSCS, TNFBM will be measured during participants' conventional bowel routines at home. Participants will be asked to record the time from 'suppository insertion' to 'when bowel evacuation is completed' once per week for the bowel movement completed mid-week during each week of the 6 week TCSCS pathway.

24 ABPM will be performed mid-way through the 6 weeks and during the final week of the 6 weeks of treatment in combination with the participants' bowel routine.

## Visit 19-20 OR 37 – 38: Immediate Post-TCSCS Assessments – Week : 13

Visit 19 or 37 (approximately 3 hours):

After the 6 weeks of TCSCS, all participants will complete 1 visit at ICORD including UDS assessments and a SCI severity assessment (ISNCSCI). Please see description of Assessments for details.

Visit 20 or 38 (approximately 1 hour):

A series of questionnaires on low urinary tract function, bowel function, cardiovascular function and sexual health will be conducted by telephone or video conference call (considering the present COVID-19 pandemic environment). The questionnaires are listed below and details can be found in the Description of Assessments Section.

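### The 4-day advice against erectile-dysfunction drugs covers only the urodynamic tests and omits anorectal manometry, which has the same stimulation, dysreflexia monitoring and management

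*Protocol*

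**What the plan says.** **The advice.** Known Study Risks/Harms asks participants not to take three named erectile-dysfunction drugs for "4 days before the urodynamic tests as this could cause a drop in blood pressure requiring medical attention". The possible fall in pressure is the only reason given, and UDS is the only procedure named. An earlier bullet in the same section, on exposure and privacy, names UDS and ARM together.

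**Monitoring and management.** The Cardiovascular monitoring section sets up beat-by-beat blood pressure recording to detect events "such as autonomic dysreflexia, during UDS and ARM (with and without TCSCS". It then gives one route for any episode, without separating the two procedures: "Autonomic dysreflexia will be resolved with the implementation of an established clinical management protocol in accordance with the Consortium of Spinal Cord Medicine". The visit plan for Visits 4, 5 and 6 also applies stimulation (TCSCS) and cardiovascular monitoring to both.

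**Drug step.** The Treatment section, after three non-drug steps, says that "if arterial blood pressure is still elevated and it is above 150 mmHg the next step in management is initiation of pharmacological agents". The agents listed are nifedipine, captopril and "Nitrates (1-2 inches applied to non-hairy part of chest". Nothing limits this step to UDS.

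**Visit order.** Pathway 1 starts with UDS 1 at Visit 4, "followed by a second session of Urodynamics (UDS 2, Visit 5), and ARM (Visit 6". In Pathway 2, "individuals will start with ARM (Visit 4), followed by Urodynamics (UDS 1, Visit 5", with UDS 2 at Visit 6. The three visits fall in Weeks 4 to 6, and the spacing between them is not stated. The next UDS comes in Week 13, when "all participants will complete 1 visit at ICORD including UDS assessments".

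**The concern.** The protocol regards recent intake of these drugs as medically relevant before a pressure-monitored procedure. It then runs a second procedure of that kind and leaves it out of the advice, without giving a reason.

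The protocol's own account of dysreflexia does not set the bowel apart. The Background literature review lists bowel stimuli beside bladder and sexual stimuli as frequent triggers of severe episodes. The section on 24-hour blood pressure monitoring calls the bowel routine a common trigger.

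A participant could therefore follow the advice exactly and still come to ARM having recently taken one of the drugs. What is at stake is the safety of individual participants, not the validity of any result.

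**Working it through.** The protocol gives no figure to reproduce. The check compares sections and counts days.

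**1. UDS and ARM side by side**

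| Item | UDS | ARM | Section |
|---|---|---|---|
| Stimulation during the procedure | yes | yes | Visits 4,5,6 |
| Dysreflexia monitoring | yes | yes | Cardiovascular monitoring |
| Management of an episode | one shared route | one shared route | Cardiovascular monitoring |
| Pressure-lowering drugs available | not restricted | not restricted | Treatment |
| 4-day drug advice | yes | not named | Known Study Risks/Harms |

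**2. Other places that might close the gap.** No eligibility criterion names these drugs. Inclusion criterion 14 requires stable dosage for 4 weeks before participation, and screening records concomitant medication. Both help in part, but neither deals with as-needed intake shortly before the ARM day.

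**3. Does the UDS window happen to cover ARM?** Assume that visits fall on different days and that the advice covers the 4 whole days before each UDS. Call the ARM day 0.

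*Pathway 2 (ARM first).* Let UDS 1 be d days after ARM. The advice runs from day d − 4 to day d − 1, so the advised drug-free days before ARM number max(0, 4 − d):

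| d | Calculation | Days before ARM |
|---|---|---|
| 1 | 4 − 1 | 3 |
| 2 | 4 − 2 | 2 |
| 3 | 4 − 3 | 1 |
| 4 or more | 4 − 4, or floored at 0 | 0 |

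The maximum is 3. UDS 2 comes later still, so its window adds no day before ARM.

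*Pathway 1 (ARM last).* Let UDS 2 be e days before ARM. Its window runs from day −e − 4 to day −e − 1. It overlaps the 4 days before ARM by max(0, 4 − e) days: 3, 2, 1 or 0 for e = 1, 2, 3, or 4 and above. These are always the earlier days. From the end of UDS 2 until ARM, intake is allowed, so no advised abstention runs up to the ARM visit itself. The UDS 1 window lies earlier and adds nothing, and the next UDS is not until Week 13.

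**Result.** In neither pathway, at any spacing on different days, does the advice as written give 4 continuous drug-free days up to ARM.

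**The case against.** **The restriction to UDS may be deliberate.** The protocol treats UDS as the riskier procedure. Known Study Risks/Harms describes UDS as a common cause of dysreflexia at T6 and above, and says that participants will not be left alone during it because of the risk of high blood pressure. The Urodynamics section sets a stopping limit of 180/110 mmHg, whereas the ARM section sets none and describes a simple, well-accepted test. All of this stands: no passage calls dysreflexia common during ARM. It explains why UDS comes first in the authors' minds. It gives no reason for exempting a procedure that they chose to monitor and manage in the same way.

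**The link to the dysreflexia drugs is not written down.** This also stands. The advice cites only a fall in pressure, and the Treatment section mentions no interaction. Connecting the two is an inference from the shared management route. The inconsistency between UDS and ARM does not need that link, because the stated reason for the advice does not depend on which of the two monitored tests follows.

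**The same logic would reach the mapping visit and every long-term session.** If so, abstention would be close to continuous for 6 weeks in a trial with a sexual-function objective. The line can be drawn on the text: the section that sets up dysreflexia monitoring names UDS and ARM and no other procedure.

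**The physician may already know.** A reader might infer that the attending physician would reach the drug step unaware of recent intake. The documents do not support that. Management follows external guidelines that are not at hand and may include such a check, and the consent pages, where instructions to participants may appear, were removed.

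**Conclusion.** The point holds as a minor, nearly free safety improvement. The drug advice names UDS only, and the visit order does not make up for the omission: at most 3 advised days before ARM in Pathway 2, and no advised abstention running up to ARM in Pathway 1. This assumes visits on different days. The protocol does not state the spacing.

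Three larger readings should be resisted.

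- With one ARM for each of 40 participants, a reader might say that 40 ARM visits are exposed. That count includes women and non-users. The number of users is not given, so no count of affected participants can be stated.
- A reader might say that Pathway 1 leaves none of the 4 days before ARM covered. With close spacing, up to 3 of them can fall in the window before UDS 2. What is missing is coverage of the days nearest to ARM.
- A reader might conclude that ARM carries the same dysreflexia risk as UDS. The protocol describes only UDS as the common trigger.

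No endpoint, sample size, error rate or analysis is affected.

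**What to change.** In the Known Study Risks/Harms sentence, add *and the ARM visit* after the reference to the urodynamic tests, so that the same 4 days apply before both. Optionally, confirm last intake of these drugs at the start of the ARM visit, before any stimulation. Asking then delays no treatment. If the cited guidelines already include such a check, this only moves it earlier. Nothing here requires a new question at the UDS visits, which the advice already covers.

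The cost is one phrase and, if the option is taken, one question per participant. Advised abstention before the short-term tests rises from at most 2 × 4 = 8 days to at most 3 × 4 = 12 days, and by less where windows overlap. An ARM visit may occasionally need rescheduling. The change applies equally to the moderate and intensive groups.
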